### Confounders

Confounders such as age, sex, education, employment status, smoking, diet, cardiovascular risk factors, depression, years at home address will be accounted for.

### Longitudinal follow-up

Participants will be followed up through a second wave of data collection in conjunction with the second wave of NICOLA-HCAP in 2026. Participation in wave 2 will be offered to any surviving members of the wave 1 sample who are not living in a nursing home, can provide written informed consent and have been deemed to have the capacity to consent. In addition, a random sample of new participants (≥65 years) who have been recruited to NICOLA and subsequently NICOLA-HCAP through a sample refresh and who meet the inclusion/exclusion criteria will also be invited to participate. The same study procedures outlined above will be followed. This will provide a longitudinal integrated dataset which includes: (1) physical activity behaviour; (2) environmental exposure data; (3) geospatial environmental data; (4) biological data and (5) a range of cognitive health outcomes. Longitudinal high-resolution spatial datasets will be created facilitating investigations into the influence of the urban environment on cognitive health over time. Wave 2 of this study and NICOLA-HCAP have been planned for 2025/2026, pending the successful obtainment of funding. Please see online supplemental figure 1.

### Statistical analysis

Below we provide an overview of three statistical approaches that we will apply to the integrated data.

#### Total effect analysis

The focus of this analysis is the total effect of physical activity on cognitive function. The exposure variable will be operationalized as average daily MVPA minutes. We will assume that 7-day accelerometer measured physical activity represents the regular physical activity of a participant. The outcome variable will be operationalized as the MMSE score. We will use a directed acyclic graph (DAG) to identify our causal assumptions and a sufficient adjustment set according to d-separation rules.^50 51^ A preliminary DAG is provided in figure 4. We will employ the backdoor criterion for identification of the causal effect.^51^ This involves identifying potential confounding variables that could influence both the exposure and the outcome. Potential confounders include sociodemographic factors (age, sex, education, deprivation and marital status), capabilities (mobility, grip strength, sensory impairments) and opportunities (availability of greenspace and social relationships). By conditioning on these variables, we will be able to identify the total effect of physical activity (exposure) on cognitive function (outcome). Causes of the physical activity behaviour will be identified based on the COM-B model of behaviour.^52^ This will include physical (eg, physical or sensory impairments) and psychological capabilities (eg, previous cognitive function levels); physical (eg, access to recreation facilities) and social opportunities (eg, social support) of participants as well as sociodemographic characteristics. Multivariable linear regression models with doubly robust estimators will be used to estimate the average causal effect.^53^ As a sensitivity analysis, we will test various ways of operationalising the exposure and outcome. This will include average daily acceleration and average daily sedentary time for exposure, episodic memory and processing speed for outcome.

**Figure 4 F4:**
[figure not shown]
Preliminary directed acyclic graph for the effect of physical activity on cognitive function.

#### Mediation analysis

Associations of environmental attributes (GIS data) with lifestyle behaviours and cognitive health will be estimated using multilevel modelling in a structural equation modelling framework,^54^ which is able to account for administrative unit-level and person-level (repeated measures) clustering and is appropriate for data with different distributions.^55^ Contemporary guidelines on discerning general from specific context effects will be followed.^56^ Plausible confounders will be identified using a pre-specified conceptual framework in conjunction with rules governing appropriate covariate selection and depending on the mechanism proposed, will be modelled as either a time-non-varying covariate, moderating or mediating effect as appropriate.^57^ Measurement of cognitive function took place in Waves 1+2 of NICOLA as well as the HCAP (in 2021), (26) yielding data that is amenable to use in a latent change score mediation within a multilevel SEM framework, satisfying the temporal ordering assumption for mediation analyses.^54 58 59^ Current guidelines on reporting SEM analyses will be followed.^60^ As a sensitivity check, an alternative approach to mediation from the causal inference literature will be used to decompose the total effect of the environment on cognitive function into direct, indirect and interactive effects.^61^ Based on a bias-corrected bootstrapping test of mediation, with 2000 bootstrap samples, and assuming a small (simulated at 0.14) effect size for both the path from environment to mediator and from mediator to environment, a sample size of approximately 462 would be required for a power of 0.8.^62^ Complementary to this, to further inspect putative causal relations between mediators and cognitive function, a 2-wave latent change score model (as previously used)^63^ will be used on a subset of Wave 1 NICOLA and NICOLA-HCAP respectively. Traditional bias-corrected bootstrapping will be used to determine whether lifestyle behaviours mediate the association between environmental exposures and cognitive outcomes. We will employ two strategies to mitigate collinearity, either: (1) composite measures of collinear variables or (2) the residual error term from preliminary bivariate regressions, will be included in multiple predictor models. Missingness will be assessed and, if missing at random or completely at random, will be addressed by full information maximum likelihood estimation for the mediation analyses.

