### Study procedure

After completing the battery of cognitive tests, NICOLA-HCAP participants will be invited to participate in the current study by the NICOLA-HCAP researcher if they meet the inclusion criteria detailed above.A short description of the current study and what is expected of potential participants will be verbally provided by the NICOLA-HCAP researcher, and participants will be provided with a paper copy of the participant information sheet and participant invitation letter.Potential participants will have the opportunity to ask the NICOLA-HCAP researcher questions relating to any element of the current study.At this stage, if participants verbally agree to participate in the current study, the NICOLA-HCAP researcher will provide them with a study pack. This pack contains two consent forms, two monitors (an accelerometer and a GPS device on an elasticated waist band), a monitor instruction sheet and a GPS charger.If the potential participant requires more time to consider their participation, the NICOLA-HCAP researcher will only leave a study pack if the participant agrees that this is acceptable. It should be noted that leaving a study pack does not mean that the individual must participate in the current study, they are free to refuse participation or to withdraw at any time without providing a reason.Participants will have the opportunity to read through the information and to familiarise themselves with the project before a project researcher contacts them via telephone approximately 1–3 days after their NICOLA-HCAP visit. This call aims to: (1) ensure that the participants understand the procedures; (2) provide participants with an opportunity to ask questions and (3) ensure that a standardised measurement approach is undertaken. If at this stage the participant wishes to withdraw, they are free to do so, and the researcher will arrange collection of their study pack. If they are willing to participate, they will be asked to wear both monitors on the elasticated waist belt for seven consecutive days.If a participant did not agree to a study pack being left at their home but they did agree to a researcher phoning to discuss their potential participation, the researcher will make contact via telephone 1–3 days following the NICOLA-HCAP study. If at this stage the participant agrees to participate, a researcher will arrange a time to drop/post a study pack to their home.During the 7-day monitoring period, participants will be asked to wear the monitors on an elasticated belt during waking hours (ie, remove to go to bed). The devices may also be removed when undertaking any water-based activities. To reduce participant burden, the research team will only contact participants once by telephone to ensure that they are not having any issues and to answer any questions that they might have. The participants will also have been provided with a telephone number to enable them to contact the research team on with any queries they may have.Following the 7-day monitoring period, the research team will contact the participant to arrange a date/time to collect the monitors along with one signed consent form from the participant’s home.Alternatively, if the participant would prefer to have a postal return the research team will provide a pre-paid return package.

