### Physical activity and sedentary behaviour (accelerometry) mediating and exposure variables

Participants will be asked to wear an ActiGraph GT3X or a GT3XP-BTLE accelerometer on the right hip for seven consecutive days to measure physical activity (ie, light, moderate and vigorous) and sedentary (eg, amount of time spent sitting) behaviour. Following wear, the raw accelerometry data will be downloaded, screened, cleaned and processed using ActiLife 6 Software (ActiGraph, Pensacola, Florida, USA). Accelerometer data will be collected at 100 Hz, and processed data will be stored as ‘activity counts’ per 15 s epochs. The activity intensity of each 15 s epoch will be classified using the Copeland & Esliger cut points (sedentary behaviour ≤99, light physical activity 100–1040 and moderate-to vigorous physical activity ≥1040).^41^ To be included, a participant needs at least 3–5 days of at least 8–10 hours of wear time. Non-wear is defined as a period of 120 min.^42^ The data will be scored, and specific cut-points will be applied as follows: sedentary behaviour ≤99; light physical activity 100–1040 and moderate-to vigorous physical activity ≥1040.^41^

Derived physical activity variables from accelerometry will include:

Average acceleration (activity counts).Average acceleration per day.Average acceleration per weekday.Average acceleration per weekend day.The most active part of the day.Average acceleration in the most active hours.The least active part of the day.Average acceleration in the least active hours.Time spent in sedentary behaviour.Time spent in light physical activity.Time spent in moderate physical activity.Time spent in vigorous physical activity.

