#### Compositional data analysis

To analyse the relative proportion of time spent in different activities, we will also investigate the association between movement behaviour (exposure), urban green and blue space (exposure) and cognitive health (outcome) by implementing a compositional data analysis approach. Having access to accelerometry, GPS and GIS enable investigations that are focused both behaviourally (part 1) and geographically (part 2).

Part 1—behaviour focused; will examine:

(1a) during waking hours, how is time spent in one movement behaviour relative to others (ie, sedentary behaviour, light physical activity and moderate-to-vigorous physical activity) and associated with cognitive health?

(1b) how does the risk of cognitive decline change, when the time spent in specific movement behaviours (ie, sedentary behaviour, light physical activity and moderate-to-vigorous physical activity) are redistributed across waking hours?

Part 2—addition of geographical location (green and blue space); will examine:

(2a) during waking hours how is time spent in one movement behaviour relative to others (ie, sedentary behaviour in green and blue space, sedentary behaviour everywhere else, light physical activity in green and blue space, light physical activity everywhere else, moderate-to-vigorous physical activity in green and blue space and moderate-to-vigorous physical activity everywhere else) and associated with cognitive health?

(2b) how does the risk of cognitive decline change, when the time spent in specific movement behaviours (ie, sedentary behaviour in green and blue space, sedentary behaviour everywhere else, light physical activity in green and blue space, light physical activity everywhere else, moderate-to-vigorous physical activity in green and blue space and moderate-to-vigorous physical activity everywhere else) are redistributed across waking hours?

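### The monitors are worn after the HCAP tests, so the mediation section's claim that temporal ordering is satisfied does not hold for device-measured activity and GPS

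*Protocol article*

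**What the plan says.** The *Mediation analysis* section notes that cognition was measured at NICOLA Waves 1 and 2 and at HCAP. It proposes a latent change score mediation on those data and describes them as "satisfying the temporal ordering assumption for mediation analyses". The claim is not limited to particular mediators.

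The mediators to be tested are lifestyle behaviours. Device-measured activity is among them: the accelerometry section is titled "Physical activity and sedentary behaviour (accelerometry) mediating and exposure variables", and the Introduction names physical activity as a possible mediator between urban environment and cognition.

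The *Study procedure* section fixes the order of measurement:

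- "After completing the battery of cognitive tests, NICOLA-HCAP participants will be invited to participate in the current study"
- then "a project researcher contacts them via telephone approximately 1–3 days after their NICOLA-HCAP visit"
- and, if willing, "they will be asked to wear both monitors on the elasticated waist belt for seven consecutive days".

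The *Total effect analysis* section takes average daily MVPA minutes as exposure and MMSE, part of the same HCAP battery, as outcome. It states that conditioning on its confounders identifies the causal total effect. The second wave, which would supply a later cognitive score, is "pending the successful obtainment of funding" (*Longitudinal follow-up*).

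**The concern.** Mediation needs the mediator to come before the outcome. Having cognition at several time points orders cognition against itself. It says nothing about where the mediator falls. Here the device record comes after all three cognitive measurements on which the ordering claim rests.

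An older person whose cognition is already lower at the HCAP visit may move less in the following week. That yields the same association as activity protecting cognition. With this order of measurement, the plan would report it as a mediated pathway or a causal total effect, and causal mechanism is the study's stated purpose.

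**Working it through.** **1. Order of measurement, from the article's own sections.**

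| Step | Measurement | Source |
|---|---|---|
| 1 | Cognition at NICOLA Waves 1 and 2 | *Mediation analysis*; *Study population* says HCAP participants had already taken part in NICOLA Wave 2 |
| 2 | HCAP battery, including MMSE | *Study procedure*; HCAP measures table |
| 3 | Telephone call about 1–3 days later, then seven days of accelerometer and GPS | *Study procedure* |
| 4 | Second-wave HCAP, 2025/2026, funding pending | *Longitudinal follow-up* |

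The ordering claim rests on steps 1 and 2 only. The device mediator is step 3. The only outcome after it is step 4, which the claim does not cite. The mediation section dates HCAP to 2021, whereas *Participant recruitment* starts in February 2022. On either date the tests come before the monitors.

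**2. The plan's own figure.** The mediation section gives about 462 participants for power 0.8, using a bias-corrected bootstrap with 2000 resamples and 0.14 on each path. The second path is worded as running from mediator to environment; it is read here as mediator to outcome. Simulation with unit residual variances, two-sided alpha 0.05 (assumed; not stated) and 1200 replicates gives power 0.787 at n=462. The figure is reproduced.

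**3. The same test with reverse causation only.** Environment to activity is 0.14, cognition to activity 0.14 (assumed), activity to cognition zero, and there is no adjustment for earlier cognition.

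| n | Declared mediated, true mediation | Declared mediated, reverse path only |
|---|---|---|
| 462 | 78.7% | 79.2% |
| 400 | 69.8% | 71.2% |

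The mean indirect effect at n=462 is 0.0196 under true mediation and 0.0191 under the reverse path. The test does not distinguish the two.

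**4. With adjustment for earlier cognition, as a change-score model allows.** Assumed: stability 0.7, reverse path r from HCAP-time cognition to activity, no effect of activity, all variables of unit variance, n=400.

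- Earlier cognition c0. HCAP cognition c1 = 0.7·c0 + e, so var(e) = 1 − 0.49 = 0.51.
- Activity A = r·c1 + u, with var(u) = 1 − r².
- Given c0: cov(A, c1) = 0.51r and var(A) = 0.51r² + 1 − r².
- Coefficient of A adjusted for c0: b = 0.51r / (0.51r² + 1 − r²). It is the same whether the outcome is c1 or the change c1 − c0.

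For r = 0.2:

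- b = 0.102 / (0.0204 + 0.96) = 0.102 / 0.9804 = 0.104
- partial correlation ρ = 0.102 / √(0.51 × 0.9804) = 0.144
- expected t ≈ 0.144 / √(1 − 0.144²) × √397 ≈ 2.90
- share significant ≈ Φ(2.90 − 1.96) = Φ(0.94) ≈ 0.83

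With no adjustment the coefficient is 0.20, so adjustment about halves it. Since r is not in the documents, the range from the same formulas is:

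| r | adjusted b | ρ | share significant, n=400 |
|---|---|---|---|
| 0.10 | 0.051 | 0.072 | 0.30 |
| 0.14 | 0.072 | 0.100 | 0.52 |
| 0.20 | 0.104 | 0.144 | 0.83 |
| 0.30 | 0.160 | 0.219 | 0.99 |

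Setting var(u) = 1 instead changes little: for r = 0.2, b = 0.102 / 1.0204 = 0.100.

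**5. After the fix.** With second-wave cognition as outcome, first-wave activity as mediator and first-wave HCAP cognition adjusted for, large-sample regression (1,000,000 records, stability 0.7 again) gives a spurious coefficient of about 0.000 for r from 0.10 to 0.30.

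**The case against.** **Habitual activity.** The total effect section openly assumes that the seven-day record represents regular activity, so a gap of days may seem unimportant. That assumption concerns level, not direction: regular activity may itself reflect current or earlier cognition. It lessens the weight of the short gap but does not establish order.

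**Not every mediator is affected.** This stands. Social activity is one of the lifestyle behaviours, and social networks and support come from NICOLA Waves 1 and 2, before HCAP. A reader might infer that the ordering claim is false throughout; it fails only for device-measured variables.

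**Prior cognition may already be adjusted for.** This also stands. The confounder list is open, the adjustment set is to come from a preliminary DAG, and previous cognitive function is named as an example cause of activity. A reader might infer that it is left out; the text does not show that. Nor would including it settle the matter. If activity depends only on earlier cognition, the problem is confounding and adjustment removes it. If activity responds to cognition at the time of HCAP, adjustment leaves the residual in step 4.

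**The compositional questions.** Questions 1b and 2b ask "how does the risk of cognitive decline change, when the time spent in specific movement behaviours" are redistributed. A reader might infer that their outcome is a single HCAP score, which carries no decline. The section does not fix the outcome, and earlier NICOLA cognition, an informant measure of decline and a possible second wave all exist. The wording is loose, but no error is shown.

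**Conclusion.** The ordering claim is wrong as written for accelerometer and GPS mediators at the first wave. The same order of measurement undermines causal identification of MVPA on MMSE. This follows from the article's own sections and needs no outside figure. It is a positive statement contradicted by the stated procedure, so it is not a detail left to an analysis plan.

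The size of any bias is not known. The coefficient of about 0.10 and the 83% rest on an assumed reverse path of 0.2 and stability of 0.7, with activity responding to HCAP-time cognition. A reader might go further and conclude that reverse causation accounts for the whole planned effect. The documents do not support that: they give no reverse path, and their 0.14 is a per-path mediation value tied to about 462 participants. Under the step 4 assumptions, a path of roughly 0.3 would be needed to reach 0.14 after adjustment.

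**What to change.** 1. In *Mediation analysis*, restrict the ordering sentence. For example: temporal ordering can be met for mediators measured at NICOLA Waves 1 or 2, before HCAP; it is not met at the first wave for accelerometer or GPS variables, which are recorded after HCAP. Keep the pre-HCAP latent change models for the earlier-wave mediators.
2. For device-measured activity and GPS, make first-wave device data against second-wave HCAP cognition, adjusted for first-wave HCAP cognition, the analysis that carries causal or mediation language. State that it depends on second-wave funding.
3. In first-wave analyses, including the total effect analysis, put NICOLA Wave 1/2 cognition explicitly in the adjustment set and report the results as cross-sectional associations.
4. In questions 1b and 2b, speak of decline only where the outcome is a measured change; otherwise speak of a difference in cognitive score.

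Items 1, 3 and 4 cost wording and a covariate from the earlier NICOLA waves. Item 2 costs time: causal claims for device-measured activity wait for the second wave, or are softened if it is not funded. It may also cost numbers. The second-wave sample includes newly recruited participants without first-wave device data, so fewer than the stated 400 may contribute. The near-zero bias in step 5 further assumes that first-wave cognition is measured without error, so its limits should be reported with the result.

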#### Sample size

The NICOLA-HCAP assessment will be offered to the NICOLA participants aged ≥65 years, with a random sample of 50% of those living alone (n=1695) and a random sample of 50% of those living in a partnership or with a sibling etc. (n=2401). The response rate for the NICOLA-HCAP is expected to be approximately 80% and assuming a selection rate of ~1 in 3 to achieve the target of 1000 participants. Of 1000 NICOLA-HCAP participants, there is an anticipated uptake to the current study of ~40% (n=400).

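### The bias-corrected bootstrap chosen to decide mediation exceeds 5% false positives when one path is null and the other is about 0.14 to 0.26; tests that hold about 5% have power of about 0.70 to 0.745 at 462, not 0.8

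*Protocol article*

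**What the plan says.** All of this is in the Protocol article, Statistical analysis, Mediation analysis.

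- **Power basis.** The test and effect size are named: "Based on a bias-corrected bootstrapping test of mediation, with 2000 bootstrap samples, and assuming a small (simulated at 0.14) effect size". The effect applies to two paths: "assuming a small (simulated at 0.14) effect size for both the path from environment to mediator and from mediator to environment". The second path is read here as mediator to cognitive outcome, since that is the path a mediation test needs. The result is "a sample size of approximately 462 would be required for a power of 0.8".
- **Decision rule.** "Traditional bias-corrected bootstrapping will be used to determine whether lifestyle behaviours mediate the association between environmental exposures and cognitive outcomes".
- **Model.** A multilevel structural equation model, "which is able to account for administrative unit-level and person-level (repeated measures) clustering". The power statement itself gives no clustering allowance.

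The section states no significance level or interval level for this test, and it names no other bootstrap interval or joint-significance test. A decomposition into direct, indirect and interactive effects is planned as a sensitivity check.

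**The concern.** A bias-corrected interval moves its limits according to how far the bootstrap distribution is off-centre from the estimate. For a product of two paths, that shift can push the interval clear of zero too often when one path is truly zero and the other is not. The test then looks more powerful than an alternative that keeps its level, and part of the stated power is bought with extra false positives.

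The case is plausible in this study. Activity may affect cognition while a particular environmental layer does not affect activity. A false positive there is a false claim of mechanism, and mechanism is what the study sets out to learn. How many of the tested pathways have this form cannot be known from the article.

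**Working it through.** **Inputs from the Mediation analysis section.** Bias-corrected bootstrap with 2000 resamples; both paths a = b = 0.14; n = 462; stated power 0.8.

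**Assumptions.** Two-sided 0.05, that is, a 95% interval excluding zero. One exposure, one mediator, one outcome, independent rows, ordinary least squares for each path. The scale of 0.14 is not stated, so two versions were run: standardised paths, and slopes with unit residual SD. Each setting used 12,000 to 20,000 data sets, giving a simulation standard error of about 0.003 to 0.004 for power and about 0.002 for rejection rates.

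**Rules compared.**
- Bias-corrected: z0 = Φ⁻¹(share of bootstrap products below the estimate); limits at the Φ(2·z0 ± 1.96) quantiles.
- Percentile: limits at the 2.5% and 97.5% quantiles.
- Joint significance: both a and b individually significant.
- Sobel: normal-theory test of the product.

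**Step 1: the plan's own figure (n = 462, a = b = 0.14).**

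| Test | Unit-residual slopes | Standardised paths |
|---|---|---|
| Bias-corrected | 0.788 | 0.802 |
| Percentile | 0.703 | 0.716 |
| Joint significance | 0.722 | 0.736 |
| Sobel | 0.514 | 0.530 |

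The stated 0.8 is reproduced by the bias-corrected test and by none of the others. With unit-residual slopes, a direct path of 0, 0.14 or 0.39 made no material difference (bias-corrected 0.786 to 0.788).

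Analytic check for joint significance: power ≈ [Φ(λ − 1.96)]².
- Standardised: λ = 0.14/√(1 − 0.14²) × √459 = 3.03, so Φ(1.07)² ≈ 0.735.
- Unit residual: λ = 0.14 × √459 = 3.00, so Φ(1.04)² ≈ 0.724.

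**Step 2: rejection rate with no mediation (n = 462, nominal 5%).**

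| Non-null path (other path 0) | Bias-corrected | Percentile | Joint significance |
|---|---|---|---|
| none (both 0) | 0.5% | 0.1% | 0.3% |
| 0.10 | 5.1% | not run | not run |
| 0.14 | 6.7–7.1% | 3.8–4.1% | 4.2–4.4% |
| 0.20 | 7.4–7.7% | 5.3% | 5.1% |
| 0.26 | 6.9% | 5.3% | 5.1% |
| 0.39 | 5.9–6.0% | 5.2% | 5.0% |
| 0.59 | 5.5% | 5.1% | 5.0% |

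A further run at 0.14 gave 6.6% to 7.7% for the bias-corrected test, 3.6% to 4.3% for the percentile and 4.0% to 4.4% for joint significance. The excess is therefore about 2 points at the plan's own effect size and at most about 2.7 points (7.7 − 5.0).

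**Step 3: power once the level is held.** The percentile bootstrap is slightly conservative at 0.14, so part of its gap is its own conservatism. To separate the two, the bias-corrected test was recalibrated to reject exactly 5% under the null:
- null with the non-null path at 0.14: critical value about 2.09 to 2.11 instead of 1.96, power 0.736 to 0.745;
- null with the non-null path at 0.20: critical value about 2.14 to 2.17, power 0.70 to 0.73.

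Tests that hold about 5% therefore have power of about 0.70 to 0.745 at 462. By the Step 1 formula, joint significance reaches 0.80 at about 520 (standardised) to 530 (unit residual).

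**The case against.** The strongest reply is that nothing is misstated. The article attributes 462 and 0.8 to a named, recognised test, that figure reproduces, and the analysis uses the same kind of test. The study is observational and explores plausible pathways, and a second mediation approach is planned as a sensitivity check.

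The first part stands: a reader might infer that 462 is a miscalculation, and it is not. The rest does not remove the point. The bias-corrected bootstrap is fixed as what determines whether a behaviour mediates, and the sensitivity decomposition is not described as a level-holding replacement for that decision.

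Three stronger readings are tempting and not supported:
- **That the false-positive rate is simply about 7%.** It depends on the non-null path: about 0.5% with both paths zero, 5.1% at 0.10, and 5.5% to 6% when that path is large.
- **That the excess carries into the Benjamini-Hochberg correction.** That sentence closes the Compositional data analysis section, and the article does not say that mediation results enter it or that p-values are taken from this bootstrap. The small thresholds that procedure uses were not simulated either.
- **That the same rate applies to the planned model.** The simulations were single-level with three variables. The plan is a multilevel latent-variable model with covariates, where the size of the excess is not established.

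The expected uptake of 400 against the required 462 is a separate matter and adds no weight here.

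**Conclusion.** The point holds in a limited form. At the plan's own effect size, the chosen decision rule exceeds the conventional 5% when one path is null: about 6.6% to 7.7% for a non-null path of about 0.14 to 0.26, and less or nothing elsewhere. Against tests that hold about 5%, power at 462 is about 0.70 to 0.745, roughly 5 to 10 points below the stated 0.8. The excess is modest, but it favours positive findings and is easily avoided.

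This rests on two-sided 0.05, which is assumed because none is stated (it does reproduce the article's figure), on independent participants, and on a single-level model with one exposure, mediator and outcome.

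**What to change.** - Make the percentile bootstrap, or the joint-significance test with a Monte Carlo interval, the rule for deciding mediation. Name the interval level.
- Keep the bias-corrected interval as a supplementary result if wanted.
- Restate the power as about 0.70 to 0.74 at 462, and say that it is for a single unadjusted test with independent participants.

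The cost is a wording change and one software option, with no change to data collection. The downside is the less favourable power figure.
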